### Sample Size

This is a feasibility study and the results will be used to inform the required sample size for a well-powered randomized controlled trial. Every effort will be made to recruit as many participants as possible during the 6-week recruitment period.

### Withdrawal Criteria

There are no withdrawal criteria for this study. Participants wishing to drop out of the study can do so by returning to the website to turn off their messages. The termination of messages will be the proxy measure of dropout rate.

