### Study Intervention

#### Intervention Group

The study website will enable participants to create the messages they wish to have sent to their mobile phones, at the times they schedule. These messages might relate to their strategies to reduce alcohol consumption or to keep safe during and after drinking. By default, the messages will be repeated weekly based on the initial day of the week and time specified by the participant. Participants will be able to create once-only messages by entering a specific date. All messages will continue to be sent, as per the participant schedule, until they are deactivated by the participant. Participants can change their messages and schedules at any time. They will also have access to the website community pages (outlined below).

Participants who own an iPhone or Windows Phone 7 will also be able to download an application to their phone to enable them to control the messages from their mobile phone. The intervention group will have access to the intervention for six months. Figure 1 illustrates the study design.

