#### Control group

Participants in this group will have access to a simple website for 3 months, where they can post messages about any topic of interest to them and participate in community discussions. The community pages will also have links to useful websites providing information on drinking safely and participants will receive a text message as these links are updated. This group will understand that they are in the control group and, after 3 months, they will receive an email or text message inviting them to access the intervention.

There will not be a limit placed on the number of messages created by the participants or on the frequency with which these messages can be sent to their mobile phones. A log of messages sent and a log of message content/schedule changes will be recorded from the website and will inform statistics on intervention usage.

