### Primary Outcomes

Primary outcomes will be collected at 3 and 6 months and include:

1. Whether the intervention engaged the interest of the participants sufficiently to make them proactive users of the mobile phone messages.

2. The acceptability of the intervention as measured by recruitment and dropout rates.

3. Safety, assessed from participant feedback and by measuring reported website misuse such as spamming others. Participant time from sign-up to last message sent until 6 months will be measured to provide an indication of the longevity of the program.

In addition, a change in unwanted consequences reported by participants in the intervention group between baseline and 6 months will provide an indication of the longevity of the intervention.

The quantitative outcomes of interest include a change in unwanted consequences and drinking. The initial question battery of AUDIT-C, YAAPST, and ASSIST will be repeated at 3 and 6 months. In addition, an open question asking the participant if they thought they had changed their drinking behavior in the previous 3 months, and if so, what changes they had made will be asked also.

The messages created by the participants will be analyzed to gain an understanding of the self-talk of this drinking population.

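### Dropout is measured by switching messages off, but messages run until switched off: silent abandoners count as retained, controls cannot be counted before month 3, and the missing-data section defines loss differently

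*Protocol article*

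**What the plan says.** Withdrawal Criteria in the protocol article tells participants how to leave: "Participants wishing to drop out of the study can do so by returning to the website to turn off their messages". It then adopts that act as the measure: "The termination of messages will be the proxy measure of dropout rate".

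Intervention Group describes how messages behave: "By default, the messages will be repeated weekly based on the initial day of the week and time specified by the participant", and "All messages will continue to be sent, as per the participant schedule, until they are deactivated by the participant". There is one alternative to the default: "Participants will be able to create once-only messages by entering a specific date".

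Primary Outcomes lists "The acceptability of the intervention as measured by recruitment and dropout rates" as its second item. Under the third item, as an indication of how long the program lasts, it adds: "Participant time from sign-up to last message sent until 6 months will be measured". Its first item is separate and asks whether participants became proactive users.

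Control group gives controls a community website for the first 3 months, with texts when its links are updated. They are invited to use the intervention afterwards. The same section says that messages sent are logged and that "a log of message content/schedule changes will be recorded from the website", to describe usage. Neither the dropout measure nor the longevity measure is defined from the change log.

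Procedure to Account for Missing Data has its own definition of loss to follow-up: people who do not use messaging, or who leave the 3- and 6-month outcome questionnaires undone. Blinding and Randomization Allocation sets 2:1 control to intervention and gives control-group attrition as the reason.

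**The concern.** The proxy needs a deliberate act, whereas the usual way to leave an online study is to do nothing. Under the default setting, doing nothing keeps the messages running. The proxy therefore misses silent abandonment and picks up people who stop the intervention but stay in the study. Withdrawal Criteria treats stopping messages and leaving the study as one event, although they are different events with different uses.

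At stake is a listed primary outcome. Acceptability is to be judged partly from dropout, and the study exists to inform a later trial. The proxy also gives no rate for controls in the first 3 months, which is the arm and period that the 2:1 allocation was chosen to protect.

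**Working it through.** The article states no expected dropout, so there is no figure to reproduce. The check is of the rules themselves.

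**1. Set-and-forget participant.** Inputs: weekly repeat until deactivation (Intervention Group) and a 6-month horizon (Primary Outcomes), taken as 182 days. If the first message goes out on day *f*, then

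- number sent = floor((182 − *f*)/7) + 1
- day of last message = *f* + 7 × floor((182 − *f*)/7)

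Results:

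- *f* = 0: 26 + 1 = 27 messages, last on day 182
- *f* = 1: 25 + 1 = 26 messages, last on day 1 + 175 = 176
- *f* = 7: 25 + 1 = 26 messages, last on day 7 + 175 = 182

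Time to last message is thus about 6 months, whatever the number of questionnaires answered. This uses the six months of access given under Intervention Group. The abstract gives 3 months; on that reading the same person would still score the longest time available.

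**2. The two definitions applied to the same people.**

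| Participant | Withdrawal Criteria | Missing-data section |
|---|---|---|
| One default message, never returns, no questionnaires | Retained | Lost |
| Turns messages off, completes every assessment | Dropout | Not lost by questionnaires; possibly lost as a non-user of messaging |
| Control before month 3, completes the 3-month assessment | Cannot be classified: no self-scheduled message to stop | Lost, read literally, as a non-user of messaging |

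**3. Share of participants not covered before month 3.** Controls are 2/(2 + 1) = 67% of those randomised.

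**4. Direction and possible size of the bias.** Let *d* be the true share of default-message users who are lost and *q* the share of those who return to switch messages off. Reported dropout among them is *d* × *q*. Both inputs are assumptions; the article gives neither.

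| True loss *d* | *q* = 10% | *q* = 30% | *q* = 50% | *q* = 100% |
|---|---|---|---|---|
| 30% | 3% | 9% | 15% | 30% |
| 50% | 5% | 15% | 25% | 50% |
| 70% | 7% | 21% | 35% | 70% |

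The proxy matches true loss only when every lost participant switches off. Below that it is too low. People who switch off but stay in the study push the reported rate the other way, so the net error over the whole intervention arm is not determined.

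**The case against.** The strongest reply is that the missing-data section already counts questionnaire non-completers as lost to follow-up, so the silent abandoner is not overlooked everywhere. Loss to follow-up is also the term that Objectives ties to sample size for the later trial. This stands. A reader might infer that the later trial's attrition allowance will be wrong by some stated factor. The document does not support that: nothing says the message-termination rate will set the allowance, and any such factor rests on assumed inputs. What remains is that two definitions of loss coexist, and the one labelled dropout is the unsound one.

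Three further inferences also go too far.

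- *That these measures record passivity instead of engagement.* Proactive use is a separate first item under Primary Outcomes, with a usage log to inform it. A weekly reminder left running may be satisfied use, because the intervention is a pre-scheduled message. Switching off is a relevant, though incomplete, signal of acceptability.
- *That users of once-only messages become dropouts.* Withdrawal Criteria speaks of turning messages off. A dated message that has been sent has not been turned off, and the article does not say that expiry counts. The effect of such messages is on longevity, which can look short for a user who is still interested.
- *That controls receive no texts.* They receive link-update texts; what they lack before month 3 is a self-scheduled message. It is also fair to say that acceptability of the intervention concerns those who have it, and that questionnaire completion can still capture control attrition.

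Finally, this is a feasibility study, the measure is called a proxy, and the abstract places acceptability and retention among secondary outcomes. These points lower the stakes, but they do not make the proxy track dropout under the default setting.

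**Conclusion.** The concern holds as a fault of definition. For an outcome listed as primary in the body of the article, the stated rule classes a complete but silent abandoner as retained, with near-maximal longevity, and classes a fully followed participant who stops messages as a dropout. It gives no result before month 3 for two thirds of those randomised, and it conflicts with the missing-data section, whose messaging limb is itself unworkable for controls in that period.

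For silent abandoners the bias is always downward. Its size is unknown: 5% to 25% reported against 50% true loss is an illustration under assumed switch-off shares of 10% to 50%, not an estimate. No data are lost, because the questionnaires and the change log are already planned. The fault can be repaired by redefinition, and this should be done before the dropout rate is reported or used for planning.

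**What to change.** Align Primary Outcomes, Withdrawal Criteria and Procedure to Account for Missing Data as follows:

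1. Define study dropout in both arms as non-completion of the 3-month assessment, and separately of the 6-month assessment, with all those randomised as the denominator. Use this rate for planning the later trial.
2. Remove non-use of messaging from the definition of loss to follow-up.
3. Report message deactivation separately, as stopping the intervention. Keep sending follow-up questionnaires to people who only stop their messages.
4. Beside time to last message sent, report time to the last participant-initiated action from the change log. Present both, since a weekly message left running may be passive or satisfied use.

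The cost is slightly more programming on data already to be collected. The reported dropout rate will probably look less favourable.

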### Data Management

The lead researcher will design, validate, and verify the security of the databases used in this study. The SQL 2008 R2 databases will be managed by Starsoft Ltd, the writers of the software. All questionnaire data will be assigned range checks and will return instructions to the user as data items are entered. All data will be entered directly by the participants, who will enter their personal log-in and password to access their messages on the website [40].

### Data Analysis

This trial has been designed in collaboration with a senior statistician at the National Institute of Health Innovation, University of Auckland, who will continue to advise and assist with analyses of the trial data. The data from the Microsoft SQL database will be exported to an Excel spreadsheet and then imported into a statistical analysis package for integrity checks prior to analysis.

The qualitative data obtained from the messages created by the participants will be reviewed by, and discussed with, a senior academic qualitative researcher at the University of Auckland who has contributed to the theoretical underpinnings of the research design. The theory underlying this design is post-positivist, seeking to infer from a non-falsified hypothesis what is probably true or what will probably be useful. Analysis of qualitative data, namely the participant messages and feedback, will use a general inductive approach to gain an understanding of self-talk around alcohol and safety. As this is a feasibility study, participants will be asked to provide feedback on the usefulness of the intervention and on suggestions for improvement. The messages and comments will be assessed by thematic analysis using NVivo 9 from QSR International.

### Treatment Effects

The relationship between frequency of text message use and behavior change (ie, change in reported drinking and/or change in safety behaviors) will be investigated. For each group, paired *t *tests will be used to assess the treatment effect between baseline and 3 months. Change from baseline to 3 months in drinking and consequences scores will be analyzed using linear regression and the model will include group and the baseline values. To assess the effect of factors such as age, gender, and ethnicity, adjusted linear regression analysis will be conducted. And if there are sufficient participants, subgroup analysis will be conducted.

Data collected at 6 months will be analyzed according to the preceding 3-month protocol. If there are sufficient data, repeated measures analysis will be run to compare the two groups across the full 6-month follow-up. Scatter plots will be generated to show the change in scores over time. Change in consequences score will be plotted at each follow-up assessment against message intensity (volume of messages sent) and correlation between these two variables will be calculated. Alcohol/consequences data will be plotted against frequency/intensity of messaging to give an indication of the messaging relationship on outcomes.

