### Inclusion Criteria

Participants will be between 18–34 years, have experienced at least one unintended consequence from drinking in the previous 3 months as measured by the selected Screening Test: Young Adult Alcohol Problem Severity Test (YAAPST), have access to the Internet, and own a mobile phone on any plan. Non-drinkers will not be excluded from participation as they may experience unintended consequences due to their association with drinkers. Non-drinkers may socialize with drinking friends and be the “responsible” person in the group. As such, they may want to use the text message service to remind themselves of this responsibility. We did not want to exclude non-drinkers from the study as non-drinkers can be caught up in unintended negative consequences when out with drinking friends. The Alcohol Use Disorders Identification Test alcohol consumption questions (AUDIT-C) scores will identify these non-drinkers and we will control for them in the statistical analysis.

There will be no limit to the number of participants. Recruitment will remain open for 8–10 months.

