#### Consequences Measure

The YAAPST was developed for use with American university students between 18–21 years [59], and is a sensitive measure for mild alcohol-related consequences, such as hangover, feeling sick, being late for work/school, etc [60]. The YAAPST also includes items on unintended sex and driving while drunk [61-68]. The measure can be scored as a lifetime occurrence of consequences, past year frequency, or past year severity [69]. There is good reliability for recall over a 12-month period [70]. Therefore, we expect similar reliability over a shorter period of time. This study will compare consequences at baseline, 3 months, and 6 months. To make the 3- and 6-month comparisons and avoid crossover of data, we will limit each recall period to 3 months.

One of the aspects that we will look at is whether the assessment items can be reduced and still collect the data we need. The intervention sign-on process tracks the point at which potential participants drop out before sign-up and we will be reviewing this for dropout particularly at the assessment points.

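### Within-group paired t tests are labelled as the assessment of the treatment effect; the baseline-adjusted group regression planned beside them should carry that label

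*Protocol article*

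**What the plan says.** All references are to the protocol article.

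- **Treatment Effects.** For each group, paired t "tests will be used to assess the treatment effect between baseline and 3 months". The next sentence says that change in drinking and consequences scores "will be analyzed using linear regression and the model will include group and the baseline values". An adjusted regression follows, then a repeated measures comparison of the groups if data suffice. The 6-month data are to be analysed in the same way as the 3-month data, so the paired tests are repeated. The section does not say which analysis gives the treatment effect if they disagree.
- **Inclusion Criteria.** Participants must "have experienced at least one unintended consequence from drinking in the previous 3 months as measured by the selected Screening Test", the YAAPST.
- **Consequences Measure and Primary Outcomes.** The outcome uses the same instrument and window: "The initial question battery of AUDIT-C, YAAPST, and ASSIST will be repeated at 3 and 6 months", and "we will limit each recall period to 3 months".
- **Primary Outcomes.** How long the effect lasts is to be judged from one arm: "a change in unwanted consequences reported by participants in the intervention group between baseline and 6 months will provide an indication of the longevity".
- **Control group.** Controls are invited to use the intervention after 3 months.
- **Blinding and Randomization Allocation.** Allocation is 2:1, control to intervention.
- **Sample Size.** No number, effect size, standard deviation or significance level is given.

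**The concern.** A paired test in one arm uses no control data. It asks whether scores changed, not whether the messages changed them. Applied to each group, the sentence would even yield a treatment effect for the controls, who do not have the messaging function in the first 3 months.

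The entry rule makes this more than a matter of terms. People with a YAAPST count of zero are kept out at baseline, but zeros can occur at follow-up. With no intervention and no time trend, the mean in both arms is therefore expected to fall. Repeated assessment may also change reporting or behaviour, and a single-arm test cannot show that either.

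The Abstract names the 3-month change in unintended consequences as the primary outcome. The Objectives section says that the data will inform sample size calculations for the later trial. If a within-arm fall were carried forward as the effect, that trial could be planned on too large a difference and be too small.

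**Working it through.** The plan states no figure to reproduce. The check asks how much a paired test is misled when nothing works.

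**Inputs from the article:** entry at one or more consequences; same instrument and 3-month recall at follow-up; 2:1 allocation.

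**Assumptions (not in the article):** two-sided 5% tests. Each person has a stable rate drawn from a gamma distribution with unselected mean m per 3 months and shape k. Baseline and follow-up counts are independent Poisson draws at that rate. There is no treatment effect and no time trend. Total N is 60, 150 or 300, with 1,500 simulated trials per cell.

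**Step 1: expected fall from selection alone.**
The chance of a zero count is p0 = (k/(k+m))^k. The mean rate of those with a zero is km/(k+m). Hence

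fall = [p0/(1 − p0)] × km/(k+m).

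- m=1, k=1: p0 = 1/2; fall = 1 × 1/2 = 0.50, from an entrant mean of m/(1 − p0) = 2.0.
- m=2, k=1: p0 = 1/3; fall = 1/2 × 2/3 = 0.33, from 3.0.
- m=4, k=1: p0 = 1/5; fall = 1/4 × 4/5 = 0.20, from 5.0.
- m=8, k=1: p0 = 1/9; fall = 1/8 × 8/9 = 0.11, from 9.0.

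The simulated falls agree (0.499, 0.331, 0.200, 0.108).

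**Step 2: how often the paired test shows a false improvement.**
Each cell gives three percentages: intervention arm / control arm / intervention arm only. The nominal rate in this direction is 2.5%. The arms are independent, so the third figure is P(intervention) × [1 − P(control)]; for m=2, k=1, N=150 it is 0.175 × (1 − 0.339) = 11.6%.

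| m, k | N=60 | N=150 | N=300 |
|---|---|---|---|
| 1, 1 | 30.3 / 48.4 / 15.6 | 56.5 / 84.5 / 8.8 | 85.1 / 98.6 / 1.2 |
| 1, 2 | 34.6 / 63.2 / 12.7 | 69.5 / 92.7 / 5.1 | 94.3 / 99.8 / 0.2 |
| 2, 1 | 12.6 / 16.1 / 10.6 | 17.5 / 33.9 / 11.6 | 32.9 / 54.5 / 15.0 |
| 2, 2 | 11.7 / 17.9 / 9.6 | 22.8 / 34.3 / 15.0 | 33.7 / 59.1 / 13.8 |
| 4, 1 | 5.1 / 6.3 / 4.8 | 6.3 / 10.0 / 5.7 | 9.3 / 13.7 / 8.0 |
| 4, 2 | 5.8 / 5.7 / 5.5 | 6.9 / 8.7 / 6.3 | 8.7 / 13.9 / 7.5 |
| 8, 1 | 3.4 / 3.7 / 3.3 | 5.0 / 4.0 / 4.8 | 3.8 / 4.9 / 3.6 |
| 8, 2 | 3.3 / 3.9 / 3.2 | 2.9 / 4.6 / 2.8 | 4.6 / 4.5 / 4.4 |

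The few cells where the control figure is slightly the lower one are within simulation error.

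**Step 3: larger arms.** A separate run of the same kind of model (mean 2, correlation 0.50, controls twice as many) took intervention arms of 50, 100 and 200. The intervention test was falsely significant in 21%, 36% and 61%, the control test in 37%, 61% and 90%, and the intervention test alone in 14%, 14% and 6%. At mean 6 the intervention-arm rate was about 3% to 4%.

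**Step 4: the regression already planned.** In the 24 cells of the table, the regression of change on group and baseline rejected in 3.8% to 5.4% of trials (nominal 5%). Both arms pass the same entry rule, so the selection effect cancels in the group coefficient.

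**The case against.** The strongest reply is that the remedy is already in the plan. The sentence after the paired tests gives the baseline-adjusted group comparison, and order of precedence is often left to an analysis plan, which is not shown. This is a feasibility study. The numbered primary outcomes are engagement, acceptability and safety, and no success threshold or go/no-go rule rests on a paired test. All of this stands, and it limits the severity. It does not remove the fault, because the article does more than stay silent on precedence: it attaches the treatment effect to the wrong test.

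Three stronger readings are tempting, and the article does not support them.

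- *The trial has no valid test of effect.* It has one, in the next sentence.
- *The risk of a false claim of benefit is 20% to 60%.* That is the error rate of one arm's test, under low assumed scores. The controls' test is run too and is affected at least as much, so the contrast that would be misread as benefit is rarer. The Consequences Measure section says that the YAAPST is sensitive to mild events such as hangover. If entrants report many of these, a cut at one selects little.
- *Season adds to the fall.* Seasonal change has no fixed direction, and staggered entry could partly cancel it. It is uncontrolled in a single-arm test, but nothing shows that it favours improvement.

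On the 6-month sentence, the text speaks only of an indication and names no test. With controls invited to cross over, a descriptive reading of one arm is understandable. It still starts from the selected baseline and is not labelled uncontrolled.

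Carrying the last observation forward would dilute the fall but not remove it.

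**Conclusion.** The point holds as a labelling error. Within-group paired tests at 3 months, repeated at 6 months, do not assess a treatment effect, and the entry rule makes some fall expected in both arms without one.

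The size cannot be fixed from the article. Under the assumed models, false improvement in the intervention arm's test runs from near nominal (about 3% to 5% against 2.5%) when scores are high to about 20% to 60% or more when scores are low and arms are large. Significance in the intervention arm alone is about 3% to 16%. It drops to about 1% or less in the most extreme setting (mean 1, N=300), where both tests nearly always reject. These figures rest on the gamma-Poisson form, the assumed means and sample sizes, two-sided 5% tests and no time trend. The conclusion that the label is wrong rests on none of them.

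Severity: should fix. The correct analysis is already planned, and no stated decision depends on the paired tests.

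**What to change.** 1. In Treatment Effects, remove the phrase that gives the paired tests the role of assessing the treatment effect. Report within-group change descriptively, as mean change with a 95% confidence interval.
2. State there that the treatment effect is the group coefficient at 3 months from the regression of change on group and baseline value.
3. In Primary Outcomes, label the intervention arm's change from baseline to 6 months as uncontrolled and descriptive. Show the change from 3 to 6 months beside it, also labelled uncontrolled, and present neither as evidence of effect.

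The cost is wording only: no new data, participants or models.

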### Blinding and Randomization Allocation

Participants will be allocated 2:1 to the control and intervention groups, respectively, to ensure adequate numbers for study comparison. There is evidence of a high level of attrition in the control group in Internet-based interventions. Therefore, we chose the 2:1 allocation to reduce the risk of control group dropout. The researchers will be blinded to treatment allocation. Participants fulfilling the inclusion criteria will be asked to consent to the study and answer demographic, drinking, and consequences questions before gaining on-going access to the website. Participants will be randomized to each of the two groups by computerized central randomization using stratified blocks (block size = 6). Two stratification factors will be used: gender (male/female) and age (≤ 24 years and > 24 years) to ensure balance in these key prognostic factors between the intervention and control groups. Once randomized, intervention participants will receive an appropriate email with instructions and reminders for setting up and accessing their messages.

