### Procedure to Account for Missing Data

Analysis will be on an intention-to-treat (ITT) basis. Those lost to follow-up will be included in the data analysis and are defined as those not using the messaging function or those who fail to complete the outcomes measures at 3 months and 6 months. Missing data will be replaced by the last observation carried forward (LOCF) with no change assumed since the last message sent. If feasible, sensitivity analyses will be performed excluding participants with missing outcome data to assess the robustness of the study findings.

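### Under 2:1 allocation, an ordinary linear regression of change scores may give the wrong standard error for the group effect if residual spread differs by arm; a robust variance is a cheap safeguard

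*Protocol article*

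**What the plan says.** Treatment Effects, in the protocol article, fixes the between-group analysis: "Change from baseline to 3 months in drinking and consequences scores will be analyzed using linear regression". The covariates are treatment group and each participant's baseline score. The 6-month data follow the same approach. Neither the variance assumption nor the standard-error estimator is named.

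Blinding and Randomization Allocation fixes the arm sizes: "Participants will be allocated 2:1 to the control and intervention groups, respectively". It gives dropout as the reason: "There is evidence of a high level of attrition in the control group in Internet-based interventions". Procedure to Account for Missing Data then sets the rule for losses: "Missing data will be replaced by the last observation carried forward (LOCF) with no change assumed since the last message sent".

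The consequences outcome is the YAAPST, and the scoring to be analysed is not fixed. Consequences Measure says: "The measure can be scored as a lifetime occurrence of consequences, past year frequency, or past year severity".

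No alpha, power or target number is given. Under Sample Size: "This is a feasibility study and the results will be used to inform the required sample size". Under Inclusion Criteria: "There will be no limit to the number of participants".

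**The concern.** Linear regression without further qualification is usually fitted by least squares with one residual variance for everyone. With equal arms, the model SE of the group effect stays about right even when the arms differ in spread. With unequal arms that protection is lost, because the pooled variance is dominated by the larger arm while the true SE depends most on the smaller one. Here the larger arm is control.

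There are three reasons why spread might differ in this trial:

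- The scores cannot fall below zero, so a roughly proportional reduction would lower spread along with the mean.
- Response to self-written messages may be uneven, which widens spread in the intervention arm.
- The article expects high control attrition and carries the last observation forward. This puts more control participants at zero change and compresses the larger arm, even if the messages do nothing.

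The first makes the interval too wide; the other two push it towards too narrow. The abstract names change in consequences at 3 months as the primary outcome, and Objectives says the data will inform the sample size and design of the later trial. An interval of the wrong width would therefore be read by those planning that trial.

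**Working it through.** **Inputs.** From the article: 2:1 control to intervention; regression of change on group and baseline; LOCF; higher control attrition expected. The article has no standard error, SD, effect size or number to reproduce. Assumed: a two-sided 5% test, and the variance ratios, count distributions and dropout rates given below.

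**Closed form.** Take 2n controls with residual variance 1 and n intervention participants with residual variance r. Randomisation makes group and baseline roughly unrelated, so baseline adjustment hardly changes the algebra.

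- Pooled variance: (2 + r)/3.
- Model variance of the group effect: (2 + r)/3 × (1/(2n) + 1/n) = (2 + r)/(2n).
- True variance: 1/(2n) + r/n = (1 + 2r)/(2n).
- Model SE / true SE: q = sqrt((2 + r)/(1 + 2r)).
- Two-sided error when the mean difference is zero: 2(1 − Φ(1.96 q)).

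| r | q | error at nominal 5% |
|---|---|---|
| 0.5 | 1.118 | 2.8% |
| 0.8 | 1.038 | 4.2% |
| 1 | 1.000 | 5.0% |
| 1.25 | 0.964 | 5.9% |
| 1.5 | 0.935 | 6.7% |
| 2 | 0.894 | 8.0% |

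With equal arms, model and true variance are both (1 + r)/n, so q = 1 for every r. The exposure comes from combining the model with the allocation.

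**Power cost when r < 1.** Where a correct SE gives 80% power, the model SE gives Φ(1.960 + 0.842 − 1.960 q). At r = 0.8 this is 77.9%; at r = 0.5 it is 72.9%.

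**Attrition route to r > 1.** Suppose the messages have no effect, average change is zero, and those lost have exactly zero change. Each arm's variance of change then scales with the fraction retained. With assumed losses of 40% in control and 20% in intervention, r = 0.80/0.60 = 1.33, q = sqrt(3.333/3.667) = 0.953, and the error is about 6.2%. Simulations of the baseline-adjusted model with the same losses gave a somewhat smaller effect: SE 4% to 5% too small, error 5.5% to 5.8%.

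**Simulated size, even benefit, no dropout.** Assumed gamma-Poisson counts, mean 5, 100 control and 50 intervention, 4000 runs:

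| True reduction | True SE | Model SE (ratio) | HC3 SE (ratio) |
|---|---|---|---|
| none | 0.736 | 0.727 (0.99) | 0.740 (1.01) |
| 20% | 0.642 | 0.691 (1.08) | 0.660 (1.03) |
| 50% | 0.562 | 0.650 (1.16) | 0.569 (1.01) |

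At the 20% reduction, rejection was 28.5% with the model SE and 33.1% with HC3. With no effect it was 4.7% with both. When only half the intervention arm responds, for mean reductions of 10%, 20% and 30%, the ratios are 0.711/0.688 = 1.03, 0.702/0.694 = 1.01 and 0.700/0.689 = 1.02.

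**Range over scenarios.** With a different assumed count model (mean 6, stronger over-dispersion), the model SE was:

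- 6% to 20% too large for even reductions of 20% to 50% without dropout;
- from about 3% too small to 11% too large for the same reductions with LOCF losses added;
- 3% to 8% too small with no effect and heavier control loss;
- 8% to 16% too small under uneven response.

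HC3 stayed within about 5% of the true SE throughout.

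**The case against.** The strongest reply is that the article does not say one common variance is assumed and does not rule out robust errors. The choice of SE estimator is a detail that a condensed article leaves to an analysis plan not shown here, and a senior statistician is to assist with the analyses. This stands in part. The silence is not an error, and the point rests on the ordinary reading of the stated model. What remains is that the stated model and the stated allocation together make the usual default fragile, and a better option is easy to name.

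Four stronger readings are tempting, and the documents do not support them:

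- *The arms must differ in spread if the intervention works.* This follows for a proportional reduction in counts. A uniform shift leaves spread unchanged, and response in half the arm leaves only a 1% to 3% error.
- *The outcome is a count, so linear regression is the wrong model.* The article speaks of scores and leaves the YAAPST scoring open. Baseline-adjusted regression is an acceptable estimator of the mean difference whichever scoring is used.
- *A working intervention will produce false positives.* With an even benefit the error is conservative: wider intervals and some lost power. The 8.0% figure needs a doubled variance with zero average effect.
- *The decision to run the later trial hangs on this interval.* No such rule is stated. The study is a feasibility trial with no defined confirmatory test.

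It is also fair to say that simulations without dropout overstate the conservative error, since the planned LOCF offsets much of it. That is why the ranges above separate the two.

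**Conclusion.** The concern holds as a modest risk of low severity. If the planned regression uses one residual variance, the 2:1 allocation exposes the SE of the group effect to any difference in residual spread, by the factor sqrt((2+r)/(1+2r)). The direction cannot be known in advance. The SE is up to about 20% too large for an even proportional benefit without dropout, less with LOCF, and about 3% to 16% too small with heavier control loss or uneven response. If the arms share one distribution, the test keeps its level.

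The closed form rests only on the allocation and the common-variance reading. The percentages rest on assumed count distributions, response patterns and loss rates, because the article gives none. The point estimate is unaffected.

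**What to change.** Keep the regression in Treatment Effects and its estimate. Add one sentence saying that standard errors, confidence intervals and p values for the group effect at 3 and 6 months, unadjusted and adjusted, use a heteroscedasticity-consistent (HC3) variance.

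The cost is one sentence and one software option. The downside is slight conservatism in small samples when the variances are equal: the HC3 SE was about 3% too large at an assumed 90 participants. HC3 is also not a complete cure. With 90 participants and an assumed strongly uneven response (half at 0.4 times and half at 1.6 times their rate), false positives fell from 8.0% to 6.3%, not to 5%. It corrects the standard error only and does not remove any bias that LOCF puts into the estimate.
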